### Study design and procedures

The proposed study is a two-arm double-blinded parallel-group RCT comparing two online interventions over a 6-month period: an intervention targeting gambling issues only versus one that contains interventions for hazardous alcohol consumption. Potential participants, who respond to the advertisement by clicking on the link or visiting the website, will be provided first with a brief description of the study prior to completing an eligibility screener. Individuals who are found to be eligible will be asked to provide contact information in the form of an email address. Subsequently, potential participants will be sent an email with a link to an online consent form. Participants will be asked to provide their telephone number and mailing address as additional contact information, as well as to provide permission for study staff to contact them via phone or mail for follow-up surveys if correspondence by email is unsuccessful. Those who complete the consent form and provide a real postal address will be sent a link to complete the baseline questionnaire and will be randomized into one of the two experimental conditions. Randomization will be stratified on age, sex, and prior use of treatment using an automatized algorithm to ensure a random distribution of prognostic indicators at baseline. To reduce attrition in the study, those who complete the baseline questionnaire and access the online intervention will receive a $10 Amazon.ca gift certificate. At 3 and 6 months post-randomization, all participants will receive an email request to complete a follow-up survey in the form of a hyper-linked web address. In addition, up to two email reminders for follow-up survey completion will be sent to participants to promote retention in the study. Furthermore, participants who complete the 3-month follow-up will be sent a $20 gift certificate and those who complete the 6-month follow-up will be sent an additional $30 gift (i.e., a total honorarium of $60 for each participant including the amount given at the baseline). Lastly, participants in both the G-only and the G + A interventions will receive an additional three emails encouraging the use of each respective intervention. See Fig. 1 for a Consort diagram summarizing the study design.

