#### G + A

The gambling plus alcohol intervention will consist of the G-only intervention as well as access to a study specific version of Check Your Drinking (CYD). The CYD contains a brief 18-item screener that has been designed to assess the quantity and frequency of drinking, and the severity of hazardous drinking [24]. Following the completion of the 18-item screener, the user is provided with a personalized report that contains normative feedback (i.e., it compares the person’s drinking with the drinking of others in the general population of the same age, sex, and country of origin, such as Canada, the U.S.A., and the U.K.). The CYD has been subjected to five randomized controlled trials from two independent research groups, all of which displayed its significant impact by reducing hazardous alcohol consumption compared to controls [24–28].

Both versions of the website contain a link to a page listing resources to contact in case of a crisis.

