#### Follow-up surveys

The 3- and 6-month surveys will employ the same measures as those assessed at baseline using a past 3-month timeframe.

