### Use of interventions

A count of participant logins into the intervention, as well as the various web pages accessed within the G-only intervention (as well as use of the CYD), will be available. These data will be used to investigate whether participants’ degree of involvement with the intervention is associated with their success at recovering from gambling or reducing gambling severity. The degree of G-only intervention use by participants will be operationalized according to the previously recommended methods [38, 39]. The number of times a participant accesses the site, the number of tools the participant uses (as assessed by page views, form completions, etc.), and the length of involvement with the site (e.g., use of the site over time) will be recorded.

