### Data analysis

The two primary hypotheses of this study, which focus on comparing outcomes between groups for gambling and drinking respectively, will be analyzed using linear mixed-effect models with random intercepts. This will allow us to use all available participant data within the models, employing a restricted maximum likelihood to handle missing data. Separate analyses will be conducted for each primary outcome variable (i.e., NODS score, mean number of day gambled in the past month, and, for drinking, the number of drinks consumed in a typical week). For secondary analyses, mixed-effects models will be conducted to examine the effect of moderators on primary variables, that is, additional fixed-effect interactions will be included in exploratory models (e.g., extent of intervention use, participants’ sex, severity of gambling and drinking at baseline, and co-occurrence of mental health concerns). In addition, secondary analyses will also examine predictors of treatment use, as well as the effect of accessing treatment on primary outcomes. The third hypothesis, comparing the potential moderating effect of reductions in drinking on gambling severity, will be examined using Hayes’s Process macro. This method uses a state-of-the-art regression-based conditional process approach [41] to estimate covariances, variances, and means. Missing data will be handled using a maximum likelihood approach. Finally, we will examine whether changes in quality of life are related to improvements in gambling outcomes.

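### The exploratory models treat self-selected intervention use as a moderator and speak of the effect of accessing treatment; neither result can be read as effect modification or as causal

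*Protocol article*

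**What the plan says.** The Data analysis section of the protocol article first sets out linear mixed models for the two between-group hypotheses. It then turns to further work: "For secondary analyses, mixed-effects models will be conducted to examine the effect of moderators on primary variables". It explains that "additional fixed-effect interactions will be included in exploratory models (e.g., extent of intervention use" is one example. The other examples are sex, gambling and drinking severity at baseline, and co-occurring mental health concerns. The next sentence adds predictors of treatment use, "as well as the effect of accessing treatment on primary outcomes".

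The Use of interventions section says what use means. "The number of times a participant accesses the site, the number of tools the participant uses" are recorded, together with length of involvement with the site. The stated purpose is to see whether "degree of involvement with the intervention is associated with their success at recovering from gambling or reducing gambling severity".

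On treatment services, the Baseline survey section asks about services used for gambling concerns, and the Follow-up surveys section repeats the baseline measures: "The 3- and 6-month surveys will employ the same measures as those assessed at baseline using a past 3-month timeframe". Treatment before the trial is handled separately, as a stratification factor: "Randomization will be stratified on age, sex, and prior use of treatment".

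**The concern.** A moderator analysis asks whether the effect of assignment differs between kinds of participant. It works because the kind is fixed before assignment, so randomization still balances the arms within each level. Sex and baseline severity meet that condition. Logins, tools used and length of involvement do not: they arise after assignment, and the participant decides them. People who use the site more are likely to be more motivated, and motivated people may improve whatever the site contains. At a given level of use, the two arms may also hold different kinds of people.

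The same difficulty applies to access to treatment. People seek help because they are motivated or because they are doing badly, so a difference in gambling between those who did and did not seek it mixes any effect of treatment with the reasons for seeking it.

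What is at stake is interpretation. A significant use term could be taken for a dose-response effect, an interaction with use for evidence of who benefits, and a treatment-access term for a treatment effect. The Discussion says the results should inform how treatments are matched to need, which is where a spurious moderator would do harm.

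**Working it through.** **Inputs from the article (Power analysis).** 280 recruited, 20% attrition, α = 0.05 (taken as two-sided). The stated follow-up number reproduces: 280 × 0.80 = 224, or 112 per arm. The article gives no figure for use, motivation or treatment access, so everything below that concerns them is assumed.

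**Model.** Unmeasured motivation U, standardized. Use = r·U + noise and outcome change = −g·U + noise, each with variance 1. Neither arm nor use has any effect on outcome. The correlation r may differ by arm. The test is ordinary least squares at the two-sided 5% level, with arm coded 0/1 and 4,000 simulated trials per setting. This simplifies the planned repeated-measures mixed model, but the source of bias is the same.

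**1. Does use falsely predict outcome?** Take r = 0.5 in both arms and g = 0.5. The slope of outcome on use is −r·g = −0.25 SD per SD, although use does nothing.
- Without an arm-by-use term: SE = √((1 − 0.25²)/224) = 0.065, ratio 0.25/0.065 ≈ 3.9, rejection about 97%. Simulation: 97%.
- With the term: the use coefficient is the slope in one arm of 112. SE = √((1 − 0.25²)/112) = 0.091, ratio ≈ 2.7, rejection about 78%. Simulation: 76%.

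**2. Does an arm-by-use term falsely show moderation?** The difference in slopes is g·(r₀ − r₁), with SE ≈ √{[(1 − g²r₀²) + (1 − g²r₁²)]/112}.

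| r, G-only | r, G + A | g | Slope difference | Approx. SE | Rejection, simulated |
|---|---|---|---|---|---|
| 0.5 | 0.5 | 0.5 | 0 | 0.129 | 5% |
| 0.5 | 0.3 | 0.4 | 0.08 | 0.132 | 9% |
| 0.5 | 0.2 | 0.5 | 0.15 | 0.131 | 20% |
| 0.6 | 0.1 | 0.6 | 0.30 | 0.129 | 62% |

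A false interaction therefore needs the use-motivation relation to differ between arms. If it is the same in both, the interaction test keeps its level, although the use slope itself remains confounded.

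**3. Does access to treatment falsely show an effect?** Assume 20% of participants access treatment, g = 0.5, and no effect of that treatment. The false-positive rate is 18%, 35% or 76% when the access-motivation correlation is 0.2, 0.3 or 0.5, and 5% when it is zero.

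**The case against.** Much of the case for leaving the text alone is sound.

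- **Status.** These models are called secondary and exploratory. No numbered hypothesis rests on use or treatment access, and the primary models do not contain them. That stands and limits the severity. It does not answer the point, because an exploratory label deals with strength of evidence, not with self-selection, which persists at any sample size.
- **Wording elsewhere.** The Use of interventions section already speaks of association. That stands, and that section needs no change. The Data analysis section goes further, to moderators and effects.
- **The interaction is not specified.** The article does not say what use will interact with; it could be time, arm, or both. That stands, so the arm-by-use figures describe one plausible version, not a stated model.
- **Content differs by arm.** G + A "will consist of the G-only intervention as well as access to a study specific version of Check Your Drinking (CYD", and a reader might infer that the use measure is structurally different in the two arms. The text does not support this: the degree of use is operationalized for the G-only content, which both arms receive, and use of the drinking module is mentioned separately.
- **Timing of treatment access.** A reader might infer that this variable certainly arises after randomization. The article does not define it. Services used during follow-up are the most natural reading, since they are asked about again at 3 and 6 months, but prior treatment is not excluded. Prior treatment would be a baseline variable, though still not randomized.
- **Missing causal method.** An article may leave this to the analysis plan, so its absence is not a fault here. The fault is in what the text does state.

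**Conclusion.** The point holds for the exploratory models only. Extent of use is put forward as a moderator although it is self-selected and accrues after randomization, and the phrase about the effect of accessing treatment claims more than a non-randomized comparison can give. Neither result could be read as effect modification or as causal.

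That bias can arise follows from the design of these analyses; its size rests wholly on assumed correlations. Use can appear to predict outcome in roughly three quarters or more of trials with no true effect. Spurious arm-by-use moderation depends on a difference between arms for which the article gives no evidence, and the 62% figure sits at the extreme corner of the assumed range.

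A reader might go on to infer that the trial's main conclusions are at risk, or that these analyses will be put forward if the main result is null. The documents support neither: the primary comparisons exclude these variables, and how results will be reported cannot be known from the plan.

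**What to change.** - Limit the moderator models to variables measured at baseline: sex, gambling and drinking severity, and mental health. Remove extent of intervention use from that list.
- Report intervention use by arm, and its relation to outcome as an association, in line with the Use of interventions section.
- Say that treatment access means services used during follow-up, if that is what is meant. Report it by arm, and replace the reference to its effect on the primary outcomes with its association with them.
- Optional: if an effect of opening the drinking module is wanted, use random assignment as the instrument (a complier average causal effect). Use of the module is recorded. This answers a different question from whether engagement with the gambling tools tracks outcome.

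The first three changes are wording and simple tabulation, and leave the conduct of the trial and the primary analysis untouched. The optional analysis costs some extra work and precision, and it assumes that assignment affects outcome only through the module.

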### Major research questions

The proposed trial will compare the efficacy of two Internet interventions: an intervention that just targets gambling issues (G-only) versus one that contains an intervention for problem drinking in addition to an intervention for gamblers (G + A). Outcome variables for gambling will measure the reduction in gambling severity and frequency of gambling. The outcome for a reduction in alcohol use will be measured by the reduction in the frequency of drinking during the past week. The primary hypotheses are:**Hypothesis 1:** For problem gamblers with co-occurring problem drinking, it is predicted that participants provided access to the G + A website will display significantly reduced gambling outcomes at the 3- and 6-month follow-ups compared to those provided access to the G-only website. For problem gamblers without co-occurring problem drinking, there will be no significant difference between those provided access to the G-only and G + A websites at the 3- and 6-month follow-ups.**Hypothesis 2:** For problem drinkers, it is predicted that participants provided access to the G + A website will display significantly reduced drinking outcomes at the 3- and 6-month follow-ups compared to those provided access to the G-only website. For participants who are not problem drinkers, there will be no significant difference in drinking between those provided access to the G-only and G + A websites at the 3- and 6-month follow-ups.**Hypothesis 3:** Problem gamblers with co-occurring problem drinking who receive the G + A intervention and reduce the amount they drink between the baseline and 3-month follow-ups will display significantly improved gambling outcomes at the 6-month follow-up compared to problem drinkers who receive the G + A intervention but experience no decrease in their drinking.

Follow-ups at 3 and 6 months were chosen as it is unknown whether the intervention will have the predicted impact, and we wished to optimize the possibility of finding an effect by employing a short-term follow-up.

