## Discussion

Many problem gamblers are also problem drinkers [13, 14, 17–20], with a lifetime prevalence as measured by nationally representative samples ranging from 45% to 73% [14, 22]. Heavy drinking often occurs while problem gamblers are engaging in gambling activities [42], resulting in increased risky gambling behavior [43–45]. Further, co-occurring problem drinking negatively impacts the treatment outcomes of problem gamblers (see the systematic review by Merkouris et al. [46]). Targeting problem drinking by problem gamblers may have the dual benefits of reducing both the problem drinking itself and of acting as a mediator for reductions in problem gambling behavior.

The proposed study seeks to determine whether providing simultaneous Internet interventions for gambling and drinking is of benefit for those with these co-occurring problems. More specifically, it will evaluate whether there is an incremental benefit to providing access to a problem drinking Internet intervention (G + A intervention) in addition to an Internet intervention for problem gambling (G-only intervention) for individuals with gambling problems who do or do not have co-occurring problem drinking. A limitation of the current trial is its short follow-up period (6-month follow-up). If the trial finds that the addition of a brief alcohol intervention to an online gambling intervention is beneficial at this time point, then future research examining any sustained impact of the intervention would be merited. The results of this study will enhance our understanding of Internet interventions for addictions in general, as well as inform how treatments can be developed and matched to the care of and needs for those with co-occurring problem gambling and drinking.

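### Hypothesis 3 compares drinking reducers with non-reducers inside the G + A arm and calls it moderation, so it cannot show that G + A, or reduced drinking, improves gambling

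*Protocol article*

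**What the plan says.** Under Major research questions, Hypothesis 3 is confined to gamblers who also have a drinking problem. The first group consists of those "who receive the G + A intervention and reduce the amount they drink between the baseline and 3-month follow-ups". The second group is set by the phrase "compared to problem drinkers who receive the G + A intervention but experience no decrease in their drinking". The prediction made for the first group is that they "will display significantly improved gambling outcomes at the 6-month follow-up". Both groups belong to the G + A arm, and membership depends on what participants do in the 3 months after randomization.

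The Data analysis section describes the test as "comparing the potential moderating effect of reductions in drinking on gambling severity, will be examined using" a named macro, whose method it calls a "regression-based conditional process approach". The Discussion gives the same variable another role: treating problem drinking may bring a second benefit by "acting as a mediator for reductions in problem gambling behavior".

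The status of the hypothesis also differs between sections. Major research questions lists it as one of three primary hypotheses. Data analysis counts only two primary hypotheses and treats this one separately.

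**The concern.** What was randomized is G-only versus G + A. Hypothesis 3 does not use that comparison. It splits one arm by later behaviour, so anything that leads a person to cut both drinking and gambling (motivation, engagement with the site, other treatment) produces a difference with no causal link between the two. Stratification on age, sex and prior treatment balances the arms, not reducers against non-reducers.

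The label adds to the problem. A moderator of the intervention is a characteristic that its effect varies over. A change that the intervention is meant to produce, and that is meant to lead on to gambling, is a mediator. The two need different models, and the plan names one in its methods and the other in its Discussion.

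At stake is the trial's statement about mechanism. The only limitation that the article gives is the short follow-up; nothing limits Hypothesis 3 to an associational reading.

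**Working it through.** **1. What one arm can estimate.** Let A be the arm (1 = G + A), M the drinking change to 3 months and Y gambling at 6 months.

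- Mediation: M = a0 + a·A + error and Y = b0 + c·A + b·M + error; the indirect effect is a·b. With A = 1 for everyone, a and c cannot be separated from the intercepts. Only b remains, and it rests on non-randomized variation in M.
- Moderation: Y = β0 + β1·A + β2·M + β3·A·M + error. With A = 1, only the sums β0 + β1 and β2 + β3 are estimable; the interaction β3 is not.

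So neither the model implied by Data analysis nor the one implied by the Discussion can be fitted to the groups that Hypothesis 3 defines.

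**2. Expected numbers.** Inputs: 280 recruited and 20% attrition (Power analysis); about 50% with problem drinking (Participants); two arms, equal allocation assumed.

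- 280 × 0.80 = 224, which reproduces the article's figure.
- G + A completers: 224 / 2 = 112. Problem drinkers among them: 112 × 0.5 = 56.
- If half reduce their drinking (assumed): 28 versus 28.
- Problem drinkers in both arms: 224 × 0.5 = 112.

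**3. Chance of p<0.05 with no causal effect.** Assume that drinking change has no effect on gambling but correlates r with 6-month gambling through a shared cause. The documents give no such r, so a range is shown. For a median split of a normal variable:

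- point-biserial correlation: pb = r × √(2/π)
- standardized difference: d = 2·pb / √(1 − pb²)
- noncentrality: d × √(28/2)
- two-sided t-test at 0.05 with 54 degrees of freedom

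| Assumed r | pb | d | Noncentrality | P(p<0.05) |
|---|---|---|---|---|
| 0.1 | 0.080 | 0.16 | 0.60 | 9% |
| 0.2 | 0.160 | 0.32 | 1.21 | 22% |
| 0.3 | 0.239 | 0.49 | 1.85 | 44% |
| 0.4 | 0.319 | 0.67 | 2.52 | 70% |

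A simulation of the same setting, taking r as the correlation with gambling after baseline adjustment and adjusting for baseline gambling (baseline to follow-up correlation 0.5 as in Power analysis; 8,000 runs per value), gave 9%, 22%, 43% and 68%, and 5% at r = 0. Adjusting for baseline gambling does not remove the problem.

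**The case against.** **What stands in the plan's favour.** Hypothesis 3 predicts a difference in outcome and makes no explicit causal claim, and the Discussion is hedged. Measuring drinking change at 3 months and gambling at 6 months gives some temporal order. Data analysis keeps this hypothesis outside the two primary ones, so the main conclusions do not depend on it. Coding and covariates may be set in an analysis plan that is not shown; Data analysis itself states no binary split. These points lower the stakes. They do not supply a randomized contrast or settle the moderator/mediator conflict: temporal order does not remove shared causes, gambling may already have changed by 3 months, and covariates cannot restore the missing arm.

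**Stronger readings that the documents do not support:**

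- *The hypothesis would probably be confirmed even if false.* The table gives 9% to 44% for r up to 0.3 and passes 50% only at about r = 0.32. The article gives no r. It supports inflation of unknown size, no more.
- *Regression to the mean would produce a false confirmation.* Problem drinking is defined by an AUDIT score of 8 or more, whereas the alcohol outcome is drinks in a typical week. If selection is on a correlated score with independent error, about 50% report a decrease by chance. Even with selection on drinks themselves, simulated regression to the mean alone made the contrast significant in only about 5% to 7% of runs. Random misclassification would dilute a real difference.
- *The macro cannot deliver the stated handling of missing data.* The article says "Missing data will be handled using a maximum likelihood approach", and nothing in it contradicts this. How it is implemented is a matter for the analysis plan.

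**Conclusion.** The concern holds as a matter of design. As written, Hypothesis 3 is a non-randomized comparison within one arm, on a self-selected post-randomization variable, labelled moderation in one section and mediation in another. It cannot estimate whether G + A works through drinking, and a significant result would not show that reduced drinking improves gambling.

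The structural conclusion needs no numerical assumption. The 9% to 70% range is an illustration. It rests on 56 completers (the article's own figures with equal allocation), an assumed even split into reducers and non-reducers, and assumed shared correlations of 0.1 to 0.4. The change should be made, but the comparisons of the randomized arms in Hypotheses 1 and 2 are not affected.

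**What to change.** In Major research questions and Data analysis, restate Hypothesis 3 as a secondary mediation analysis in problem drinkers of both arms (about 112 completers), and make the Discussion use the same term:

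- **Path:** arm → continuous change in drinks per week from baseline to 3 months → gambling at 6 months.
- **Adjustment:** baseline drinking, baseline gambling, age, sex and prior treatment. Do not adjust for 3-month gambling in the main model: it is measured after randomization and may lie on the path from early drinking change to later gambling, so conditioning on it could remove the effect sought.
- **Reporting:** the indirect effect with a bootstrap confidence interval, and a sensitivity analysis for unmeasured mediator-outcome confounding.
- **Within G + A:** report reducers versus non-reducers as descriptive and associational only.

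Problem-drinker status is fixed at baseline, so the step from arm to drinking change keeps its randomized basis.

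The cost is a change of wording and modest extra programming; no new data are needed. The step from drinking change to gambling stays non-randomized, so absence of mediator-outcome confounding remains an assumption to be stated.
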